#### The experimental task

The experimental task occurs in a novel immersive virtual reality simulation depicting an unfamiliar alien landscape. The programmed was designed with the Vizard software [28] and participants will use the HTC Vive Pro headset and controllers to interact with the created environment [29]. The task will be described as a game in which the objective is to gather fuel canisters on an unfamiliar alien planet which will provide their spaceship the power it needs to get back to Earth. The simulation presents a large desert-like outdoor landscape with features such as unusual plants, rock arches, tall mountain cliffs, and alien artifacts. Critical for the experimental task, participants will encounter aliens on the planet surface. Participants will be informed that the alien inhabitants and their planet are unusual, and events may follow different rules than on Earth. They will be told that some of the interactions with aliens may be somewhat uncomfortable. These instructions are used to trigger schemas related to pain sensitivity, reflecting experiences at dental visits, while providing a rationale for the mouthpiece the participant will wear during the entire task. Further details of the experimental task and procedures are provided by Seligman et al. [23].

#### Task phases and manipulations

From the perspective of the participant, the virtual reality “game” will appear seamlessly in each session. However, the task consists of four distinct phases: pre-exposure, conditioning, and short- and long-term learning test phases. As described below (see Table 2), the phases occur on different days, depending on pre-exposure spacing condition.

**Table 2 Tab2:** Trials in each session as a function of experimental condition

Experimental Condition	Session 1	Session 2	Session 3
No Session Spacing/ No Context Change	-12 pre-exposure trials in Context A -36 conditioning trials -12 fear recall trials	-12 fear retention trials	-------
Sessions Spaced/ No Context Change	- 6 pre-exposure trials in Context A or Context B	- 6 pre-exposure trials in Context A or Context B -36 conditioning trials -12 fear recall trials	-12 fear retention trials
No Session Spacing/ Context Change	- 6 pre-exposure trials in Context A; - 6 pre-exposure trials in Context B -36 conditioning trials -12 fear recall trials	-12 fear retention trials	-------
Sessions Spaced/ Context Change	- 6 pre-exposure trials in Context A or Context B	- 6 pre-exposure trials in Context B or Context B -36 conditioning trials -12 fear recall trials	-12 fear retention trials

*Note* Context A refers to an environment with a brighter tan color and lighting level, whereas Context B refers to an environment with a darker green color and lower lighting level.

The first trial phase, the *pre-exposure phase*, begins with a minimum of six seconds during which the participant can traverse freely in the virtual reality environment. Participants are tasked with locating fuel canisters that are scattered across the alien planet landscape. Following the initial pre-exposure trial segment, the CS^+^ _P_ is automatically displayed, accompanied by a fuel canister, at the first opportunity. The CS^+^ _P_ are alien stimuli that have small vertical motion and customized sounds. The CS^+^ _P_ and the fuel canister will appear at a fixed distance from the participant and will stay in that location for the final six seconds of the trial. Each trial therefore contains a six second segment without the CS^+^ _P_, followed by a six second segment with the CS^+^ _P_ and fuel canister. There will be twelve pre-exposure trials and during these trials the UCS is never presented.

The two between-subject independent variables are manipulated during the pre-exposure phase. The *pre-exposure context* independent variable has two levels: approximately half of the participants will complete the pre-exposure trials in a single context, whereas the other half will complete the pre-exposure trials in two contexts. Participants in the single context condition will complete all twelve pre-exposure trials in the same environment with a constant bright tan color and lighting level. Participants in the multiple contexts condition will complete six trials consecutively in the same bright tan color and lighting level as experienced by participants in the single context condition. The other six trials will occur consecutively with a darker green environment with a lower lighting level. Whether participants in the multiple contexts condition receive the six tan or green environment trials first will be counterbalanced. Next, the *pre-exposure session spacing* independent variable has two levels: no session spacing and session spacing. Participants in the no spacing condition will receive all twelve pre-exposure trials in their first experimental session. In contrast, participants in the spaced sessions condition will have six of the pre-exposure trials in their first experimental session, whereas the final six will occur at least 7 days later in a second session. The number of pre-exposure trials for all groups remains at twelve, to avoid confounding the number and spacing of trials. The allocation of trials across study sessions for each of the four between-subject conditions is displayed in Table 2.

Following the completion of the pre-exposure trials, participants will move to the *conditioning phase*, which will consist of 36 trials (12 CS^+^ _P_ trials, 12 CS^+^ _NP_, and 12 CS^-^ trials). The makeup of the conditioning trials will be the same as the pre-exposure trials, with the crucial difference that 75% of CS^+^ _P_ trials and 75% of CS^+^ _NP_ trials will co-occur with a dental startle UCS (explained below in the stimulus material section). The startle UCS will occur during the last 100ms of the trial and will co-terminate with the alien stimulus. The startle UCS will never be delivered on CS^-^ trials.

After the final conditioning trial, participants will move to the fear *recall phase*, which consists of a series of 12 test trials (4 CS^+^ _P_ trials, 4 CS^+^ _NP_, and 4 CS^-^ trials). The structure of the recall phase trials will be the same as in the prior phases. Importantly, the startle UCS will not accompany any of the alien stimuli in the fear recall phase.

Finally, all participants will return to the laboratory at least 7 days following the session that includes the conditioning phase and complete the fear *retention phase*. This phase will consist of 12 trials that have the same set up as those in the fear recall phase.

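### Table 2 contradicts the text on pre-exposure context in both spaced arms: it admits green in the single-context arm and misprints session 2 of the focal arm

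*Protocol article*

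**What the plan says.** All of this is in the protocol article, Methods, under Task phases and manipulations.

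- **Key to the contexts (note to Table 2).** "Context A refers to an environment with a brighter tan color and lighting level, whereas Context B refers to an environment with a darker green" colour and lower light.
- **Text, single context.** Participants "will complete all twelve pre-exposure trials in the same environment with a constant bright tan color and lighting level". The sentence makes no exception for the spaced arm.
- **Text, multiple contexts.** "Participants in the multiple contexts condition will complete six trials consecutively in the same bright tan color and lighting level" as the single-context group, and "The other six trials will occur consecutively with a darker green environment with a lower lighting level". On order: "Whether participants in the multiple contexts condition receive the six tan or green environment trials first will be counterbalanced".
- **Table 2, spaced without context change.** Session 1 and session 2 each read "6 pre-exposure trials in Context A or Context B".
- **Table 2, spaced with context change.** Session 1 reads the same way. Session 2 reads "6 pre-exposure trials in Context B or Context B".
- **Table 2, unspaced rows.** The row without context change has twelve trials in Context A. The row with context change lists six in A and six in B.

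The text refers the reader to Table 2 for the allocation of trials in the four between-subject conditions. The Data analysis plan names the group with both spacing and multiple contexts as the focal group and compares it with each of the other three.

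**The concern.** Pre-exposure context is one of the two randomised factors, and the article specifies it twice in ways that cannot both be followed. The disagreement lies in the two spaced rows. One is the focal arm. The other is the arm it must be compared with to isolate the effect of context among spaced participants.

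Two things are at stake. First, if the spaced single-context arm may be run in green and the unspaced one may not, a difference between them could come from spacing or from colour. That touches Hypothesis 1 as well as Hypothesis 2. Second, the focal arm's second session has no usable rule as printed. The Introduction cites animal work on the context specificity of latent inhibition, so which context a participant has seen is not a neutral detail. The article does not state the colour used in conditioning and test, so the direction of any resulting bias cannot be worked out from it.

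**Working it through.** The plan states no figure on this point to reproduce. The check compares the context sequences (first six trials, last six trials) allowed by the text with those allowed by the table.

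**Step 1. Sequences by row** (A = tan, B = green).

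| Table 2 row | Text allows | Printed cells alone | Printed cells read with the row label | Conflict with text |
|---|---|---|---|---|
| Unspaced, no change | AA | AA | AA | none |
| Spaced, no change | AA | AA, AB, BA, BB | AA, BB | BB not allowed |
| Unspaced, change | AB, BA | AB | AB | reverse order not shown |
| Spaced, change | AB, BA | AB, BB | AB | BA missing; BB possible only if the label is ignored |

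**Step 2. The spaced, no-change row.** Its label removes AB and BA. BB remains, which the text excludes and the unspaced, no-change row does not offer. The conflict therefore survives the most charitable reading.

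**Step 3. The spaced, change row.** If session 2 is always B and context must change, session 1 must always be A. But session 1 is printed as either A or B. The row cannot be satisfied as printed, so one of the two contexts in the session 2 cell must be a slip. Replacing one B by A and pairing it with session 1 under the row label gives AB or BA, which is the text's rule.

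**Step 4. Size under the charitable reading.** Assume equal allocation: 180 / 4 = 45 per arm. If a share p of the spaced, no-change arm is run in green, 45 × p participants receive green only.
- p = 0.5 (assumed even split): 45 × 0.5 = 22.5, about 22 people.
- Range for p from 0 to 1: 0 to 45.
- Green-only share at p = 0.5: 50% in the spaced single-context arm against 0% in the unspaced one.

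**Step 5. Size under a fully literal reading.** Ignore the row labels and treat each printed option as equally likely and independent between sessions (an assumption). The shares changing context, in table order, are 0, 2/4 = 0.5, 1.0 and 0.5.
- Contrast (multiple minus single) within spaced arms: 0.5 − 0.5 = 0.
- Within unspaced arms: 1.0 − 0 = 1.0.
- Pooled: (1.0 + 0.5)/2 − (0 + 0.5)/2 = 0.75 − 0.25 = 0.5.
- Under the text's rule: 1.0 − 0 = 1.0 throughout.

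**The case against.** The best defence is that the text defines the manipulation without ambiguity and each row carries a label. A row labelled as having no context change does not allow tan then green, and a row labelled as having a change does not allow green twice. An alternative between two identical options has no meaning, so the focal-arm cell is plainly a misprint. This defence largely stands, and it rules out two stronger conclusions that a reader might draw.

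- *That three of the four rows contradict the text.* The unspaced row with context change gives the same two contexts and the same trial counts as the text. A fixed tan-then-green order is only an inference from how the cell is laid out. The row is incomplete on order, not contradictory.
- *That the table undoes the context manipulation.* The contrast vanishes among spaced participants only under the literal reading of step 5: labels ignored, options equally likely and independent, misprint programmed as a rule. Even then the unspaced arms keep the full contrast, and the pooled contrast is halved, not removed. Nothing in the document shows that this was done.

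The defence does not dispose of the spaced, no-change row. Its label fixes constancy within person, not colour, so the green-only sequence remains in conflict with the text and with the unspaced row. That entry appears in both sessions and does not look like a slip of one letter.

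**Conclusion.** The point holds as a contradiction about the schedule of a randomised factor, confined to the two spaced rows of Table 2.

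The spaced single-context row is the more substantive of the two. On any reading that respects its label it still permits green-only pre-exposure, and if it were followed, spacing would be confounded with colour in the single-context arms. The figure of about 22 participants rests on equal arms and an even split, neither of which the article states. The focal-arm row is evidently a typing error, but it falls in the arm on which every planned focal comparison depends. The missing order in the unspaced, change row is a minor omission.

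The article does not show which version the virtual reality program follows, so this is a specification that is wrong as written, not evidence of a wrongly delivered experiment. It should be settled before more participants are randomised, because analysis cannot restore a contrast that was not delivered.

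**What to change.** 1. Reconcile the two spaced rows with the text so that one context rule applies to the spaced and unspaced arms at each context level. Under the text as it stands, the spaced, no-change row becomes Context A in both sessions, and session 2 of the spaced, change row becomes whichever context was not used in session 1. If the sponsor did mean to use either colour for single-context participants, the text and the unspaced, no-change row must change too, with the same mix in both arms.
2. Show the counterbalanced order in the unspaced, change row.
3. Check the REDCap and virtual reality condition files against the reconciled rule.
4. Record the context sequence actually delivered to each participant, so that any departure can be identified and reported.

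The cost is a correction to one table, a check of the condition files and one recorded variable. No extra participants or visits are needed.

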### Materials

#### Alien images

Three novel alien stimuli were created specifically for use in this virtual reality paradigm as the CS^+^ _P_, CS^+^ _NP_, and CS^-^. The stimuli were piloted with individuals between the ages of 6 and 35 to create stimulus images that are perceived as neutral and distinct from one another. Nevertheless, the three alien stimuli will be counterbalanced across participants for the CS^+^ _P_, CS^+^ _NP_, and CS^-^ to avoid confounding between alien image and stimulus type.

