To investigate Hypotheses 1b and 2b, we will conduct mediation analysis to estimate direct, indirect, and total effects associated with the pre-exposure groups on the distal outcomes of conditioned fear acquisition, recall, and retention. In parallel mediation models, the pre-exposure groups are hypothesized to impact the mediators (expected relevance and attention), which, in turn, are hypothesized to affect a given fear outcome. Note that these path models do not include within-subjects variables as the scores for the mediating variables will be obtained from the first trial of the conditioning phase, where stimulus group differences are expected to be greatest, and scores from a given distal outcome will be computed as the average of the scores across specific trials in the recall and then retention phase. If the pre-exposure variable is found to interact with stimulus type in Hypotheses 1a or 2a, then this model will be estimated separately for each stimulus type to assess if mediation is present for each stimulus.

Parameters for the mediation analyses will be estimated in Mplus with maximum likelihood estimation and percentile bootstrapping (with 20,000 bootstrap samples), with the latter used to test for the presence of indirect effects. Bootstrapping is a recommended method for mediation analysis given that indirect effects are non-normally distributed [37–39], as each indirect effect is computed as a *product* of parameter estimates.

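### Counterbalancing the aliens does not protect the per-stimulus mediation models, where alien image could be a common cause of mediator and fear; two image indicators would remove that risk

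*Protocol article*

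**What the plan says.** All places are in the protocol article.

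- **Alien images.** The stimuli were piloted across the study's age range to "create stimulus images that are perceived as neutral and distinct from one another". The section goes on: "Nevertheless, the three alien stimuli will be counterbalanced across participants for the" three roles (pre-exposed, non-pre-exposed and unpaired control). The stated purpose is "to avoid confounding between alien image and stimulus type".
- **Task phases and manipulations.** The pre-exposed stimuli are described as "alien stimuli that have small vertical motion and customized sounds".
- **Mediating variables.** Expected relevance is rated after the alien appears and before any air puff. Attention is eye tracking directed at the alien.
- **Data analysis plan, Hypotheses 1b and 2b.** The structure of the path analysis is given as follows: "the pre-exposure groups are hypothesized to impact the mediators (expected relevance and attention), which, in turn, are hypothesized to affect a given fear outcome". Mediators are scored on the first conditioning trial, and fear is averaged over trials in recall and then retention. The section notes that "these path models do not include within-subjects variables". Should the earlier tests of the mediators show that group effects differ by stimulus, "then this model will be estimated separately for each stimulus type to assess if mediation is present for each stimulus". No image term, or any other covariate, is named.

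**The concern.** Counterbalancing makes image independent of stimulus role over the whole sample, so mean differences between roles are not differences between aliens. A model fitted within one role is a different analysis: a regression between people, in which counterbalancing itself makes the image vary, with about 180/3 = 60 participants per alien. The same alien is present when the mediator is scored and when fear is scored later. If one alien drew more gaze, or looked more likely to precede something unpleasant, and was also feared more, image would raise mediator and outcome together.

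Group is randomised but the mediator is not, so nothing in the design protects the mediator-to-fear path from a shared cause of this kind. That path is one of the two factors in the indirect effect, on which the article's claim about mechanism rests. At stake is an indirect effect that appears significant although the mediator does nothing.

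**Working it through.** **Inputs from the article (Study participants).** N = 180. For mediation: required n = 106, power 0.80, indirect effect 0.15, mediator-to-outcome coefficient b = 0.3, group-to-mediator correlation r = 0.5. Alpha of 0.05 is stated for the other power calculations; two-sided 0.05 is assumed here.

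**Inputs that are assumptions.** The share of mediator variance due to image (vM), the share of fear variance due to image (vY), and the alignment ρ of the two image patterns (1 = same pattern on both, 0 = unrelated). The article gives none of these, so a range is shown.

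**Step 1: the plan's own figure.** For a test of b given group,

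n = (1.960 + 0.842)² × (1 − b²) / [b² × (1 − r²)] = 7.849 × 0.91 / (0.09 × 0.75) = 105.8, rounded up to 106.

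The stated sample size reproduces and is not affected by this point.

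**Step 2: false path when the true path is zero.** After adjustment for group, the mediator has residual variance 1 − 0.5² = 0.75. If images are balanced over groups, the shared image variance is ρ√(vM·vY), so

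false b = ρ√(vM·vY) / 0.75.

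With ρ = 1 and equal shares: 0.01/0.75 = 0.013; 0.02/0.75 = 0.027; 0.05/0.75 = 0.067; 0.10/0.75 = 0.133; 0.15/0.75 = 0.20.

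**Step 3: how often this is declared significant.** The standard error of b at N = 180 is about √[1/(180 × 0.75)] = 0.086. At a 5% share, 0.067/0.086 = 0.78, giving a two-sided rejection rate of about 0.12. At 10%, 0.133/0.086 = 1.55, giving about 0.34.

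A simulation agrees. It used 4,000 runs per setting, four groups, three balanced images, a group-to-mediator correlation of 0.5, a true b of 0, and a t test of b with and without two image indicators:

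| Image share of each variance | False b, ρ = 1 | Type I error, ρ = 1 | Type I error, ρ = 0.5 | Type I error, ρ = 1, indicators added |
|---|---|---|---|---|
| 1% | 0.013 | 0.06 | 0.05 | 0.06 |
| 2% | 0.027 | 0.065 | 0.055 | 0.05 |
| 5% | 0.067 | 0.12 | 0.065 | 0.05 |
| 10% | 0.13 | 0.34 | 0.12 | 0.05 |
| 15% | 0.20 | 0.65 | 0.20 | 0.05 |

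The false b column is from the formula; the error rates are simulated. With ρ = 0 the error stayed at about 0.05 at every share. At 1% the rates with and without indicators are the same within simulation error.

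**Step 4: from path to indirect effect.** With the planned r = 0.5, the group-to-mediator path has standard error √(0.75/180) = 0.065, so z = 0.5/0.065 = 7.7 and that path is almost always detected. A false b then passes nearly straight into a false indirect effect: 0.5 × 0.067 = 0.03, 0.5 × 0.133 = 0.07 and 0.5 × 0.20 = 0.10 at 5%, 10% and 15% with full alignment, against the planned 0.15.

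**Limit of the check.** The simulation has one mediator and a t test. The plan has two parallel mediators and a percentile bootstrap of the indirect effect. The bias formula does not depend on the choice of test, but the exact error rates may differ.

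**The case against.** The strongest case against is that nothing here is shown to be wrong. The purpose given for counterbalancing is correct as stated. The article is condensed, names no covariates at all, and may leave such terms to an analysis plan that is not shown. It excludes only within-subjects variables, and within one stimulus type image is a between-subjects variable. The images were piloted as neutral, so small effects are the natural expectation, and at 1% to 2% the harm is negligible. The large error rates need 10% or more of both variances, well aligned, and image effects that last through conditioning into recall and retention. The per-stimulus models are also conditional on an interaction.

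Most of this stands, and it rules out several stronger readings:

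- A reader might infer that image is a common cause of gaze and fear. The article reports no image effect; distinct appearance and customised sounds make one possible, not established.
- A reader might infer that the plan rules out an image term. It is silent.
- A reader might infer that Hypotheses 1b and 2b are undermined as a whole. Groups are randomised, so if images are balanced over groups the group-to-mediator path and the total effect stay unbiased. A false indirect effect also needs a non-zero group-to-mediator path.
- A reader might infer that the MANOVAs for Hypotheses 1a and 2a need an alien-role sequence factor. Three aliens in three roles give six sequences; crossed with four groups that is 24 cells of 180/24 = 7.5 people. The cost is real, and no gain has been shown.

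What does not fall is the narrower point. Counterbalancing is the only protection the article offers against image, and it does not work inside a per-stimulus model. The condition for fitting those models is the case the authors expect: the Data analysis plan anticipates larger group differences for the pre-exposed stimulus than for the others. The decision to counterbalance despite the piloting also suggests that the images were not taken to be interchangeable.

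**Conclusion.** The point holds as an improvement to the specification. In the per-stimulus mediation models the alien image varies between people and could bias the mediator-to-fear path, for expected relevance as well as gaze.

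The size rests on image shares that the article does not give. It ranges from nothing (no image effect, or no alignment), through negligible (1% to 2% of variance), to material (5%, if fully aligned) and serious (10% or more, if fully aligned). Half alignment brings the error at 5%, 10% and 15% down to about 0.065, 0.12 and 0.20. All these figures assume a true path of zero, N = 180, a group-to-mediator correlation of 0.5, and images balanced over groups.

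**What to change.** In the Data analysis plan, state that each per-stimulus mediation model includes two indicator variables for which alien served as that stimulus, in both mediator equations and in the outcome equation.

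The cost is 2 degrees of freedom per equation. With 180 people, an outcome equation with an intercept, three group terms and two mediators goes from 174 to 172 residual degrees of freedom. If the images are truly equal, that is the whole statistical price. No change to design, sample size or data collection follows. The alien-to-role assignment is set by the design but must be kept in the analysis data set; the article does not say whether it is. No change to the Hypothesis 1a and 2a MANOVAs is asked for.
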